### Intervention group

Based on the PROMPT [29] and PARADISE [28] trials, we designed the intervention of the PREMA trial as a low-threshold intervention containing the three elements CBT, case management, and eHealth-support for patients suffering from AG/PD or depression.

After randomization, primary care practices in the IG will receive online training material (therapy manuals for PCPs and MAs, intervention videos). Additionally, patients in the IG will receive online information about their disorder and trial procedures. Treatment in the IG consists of four face-to-face sessions of approximately 30 min delivered by the PCP and practice-based case management delivered by the PCP and the MA.

The four sessions delivered by the PCP include the following:
Session 1 (week 3 after treatment start): Psycho-education on depression or panic disorder. Patients learn about the symptoms and the theoretical background of their disorder as well as the treatment procedure.Session 2 (week 6): Interoceptive exposure exercises. The PCP introduces exercises that provoke the patient’s typical physical reaction. Patients learn to conquer their initial fears and to find promising solutions (activation and motivation of the patients).Session 3 (week 12): Situational exposure exercises. The patients are confronted with situations that trigger their fear or from which they withdraw. Patients with depression aim to experience pleasure in daily life activities.Session 4 (week 20): Success monitoring and relapse prevention.

Throughout the sessions, the patients are encouraged to note questions, successes, or failures online on the eHealth platform.

Case management by the MA consists of 17 telephone calls (approximately 10 min each), in which the MA asks about the patient’s well-being, completes the monitoring checklists (JAMoL [38] for patients with PD/AG, DeMoL [39] for Patients with depression), and motivates/encourages the patients. Critical responses should prompt the MA to inform the attending PCP immediately. Questionnaire responses are noted online on the eHealth platform.

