### Participation discontinuation

If a patient withdraws his/her written informed consent, the assigned study intervention will be discontinued for him/her. Severe adverse events (SAEs) are defined as a patient’s death, life-threatening event, clinically relevant severe deterioration of depression, or anxiety symptoms, acute suicidality, or adverse events that would constitute an unacceptable risk for the patient. All SAEs will be documented by the PCP and evaluated by the PI and the Data and Safety Monitoring Board (DSMB) at the principle investigator’s (PI’s) discretion to ensure safety evaluations follow the four-eye principle. If a patient completely drops out of the study, a final assessment, especially of the primary outcome, should be conducted.

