### Data handling

#### Data safety and monitoring board

An independent DSMB has been established to monitor the course of the study, recruitment, patient safety, the integrity of the trial, and, if necessary, to give a recommendation to the coordinating investigator and sponsor for discontinuation, modification, or continuation of the study. The DSMB will confer twice a year. Furthermore, the DSMB will periodically review the safety-relevant events reported to this board. The members of the DSMB are [name] [name] (Erlangen), [name] [name] (Jena), [name] [name] (Jena).

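### The SAE sentence puts DSMB evaluation at the PI's discretion, which contradicts the four-eye principle that the same sentence gives as its purpose

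*Protocol article*

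**What the plan says.** Two sections of the protocol article govern the handling of SAEs.

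- **Participation discontinuation.** The definition covers death, life-threatening events and unacceptable risk, and also "clinically relevant severe deterioration of depression, or anxiety symptoms, acute suicidality". Documentation rests with the treating physician, without distinction by arm: "All SAEs will be documented by the PCP". The events are then "evaluated by the PI and the Data and Safety Monitoring Board (DSMB) at the principle investigator’s (PI’s) discretion", and the sentence closes with the purpose, "to ensure safety evaluations follow the four-eye principle".
- **Data safety and monitoring board.** On status and remit, this section says: "An independent DSMB has been established to monitor the course of the study, recruitment, patient safety, the integrity of the trial". The board can advise the coordinating investigator and sponsor on whether the study continues, changes or stops. "The DSMB will confer twice a year". On its input, the section says that "the DSMB will periodically review the safety-relevant events reported to this board".

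Two further sections bear on how SAEs come to light. Under Intervention group, patients have four sessions with the PCP and 17 calls from the medical assistant (MA), who completes a symptom checklist; "Critical responses should prompt the MA to inform the attending PCP immediately". The abstract gives ten calls. Under Control group, patients receive standardized usual care, and no scheduled study contact of this kind is described. Under Study procedures and timing schedule, PHQ-9 and OASIS are repeated at T1 and T2, with no distinction by arm.

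**The concern.** A four-eye check protects patients only if the second reviewer's involvement does not depend on the first reviewer's choice. As worded, the PI may evaluate an SAE and also decide whether the board evaluates it. The board could then advise on continuing or stopping the trial from an incomplete set of events, without knowing that it was incomplete. The definition includes deaths and acute suicidality, so the wording matters.

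A lesser matter is how the board should read the events it does see. Some SAEs are defined by symptoms, and those are found more readily when someone asks. The schedule of asking differs between the arms.

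**Working it through.** **1. The SAE sentence against itself.** No figure in the plan bears on this point, so the check is one of reading. The sentence has three parts:

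- who evaluates: the PI and the DSMB;
- on what condition: the PI's discretion;
- for what purpose: a two-person check.

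If the condition governs *whether* the board evaluates an event, the purpose fails for every event the PI chooses not to pass on. If it governs only *how* the evaluation is arranged, the purpose can hold, but the sentence does not say so. The first is the more natural reading; the second is possible.

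**2. Does the DSMB section settle it?** It would do so if it required all SAEs to be sent to the board. It gives the board independence, a patient-safety remit and two meetings a year, but describes its input as the events reported to it. Neither section says which events must be reported. Read together, they leave the PI's discretion as the only stated condition on the board's evaluation.

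**3. Scheduled contacts by arm.** Inputs: 4 PCP sessions and 17 MA calls (Intervention group), or 10 calls (abstract).

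- Intervention arm: 4 + 17 = 21 scheduled contacts per patient, or 4 + 10 = 14 with the abstract's figure.
- Control arm: no scheduled study sessions or calls described.
- Both arms: online questionnaires at T1 and T2, including PHQ-9 and OASIS. The article states no path from those answers to an SAE report.

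**4. Can the effect on SAE counts be sized?** With equal true rates in the two arms, the ratio of recorded counts is c_I / c_C, where c_I and c_C are the proportions of true events captured in the intervention and control arms. The true SAE rate cancels. The article gives neither proportion. Taking c_I = 0.9 purely as an assumption:

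| Assumed c_C | c_I / c_C |
|---|---|
| 0.9 | 1.00 |
| 0.7 | 1.29 |
| 0.5 | 1.80 |

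The result is set entirely by the assumption and includes no distortion at all. The direction is plausible for symptom-based events, but the size cannot be derived.

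**The case against.** **On the discretion clause.** The sentence names both the PI and the board as evaluators, and its stated purpose favours the milder reading, in which discretion concerns how the board is involved. The DSMB section separately gives the board a safety remit and does not make reporting subject to the PI. The article is also condensed, so a board charter or the full protocol may set out the reporting route. What stands is that the wording is ambiguous, so it cannot be said that the board sees SAEs *only* if the PI chooses. What does not stand is the appeal to condensation: this is a rule the article states, at odds with its own purpose, and not a detail left out.

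**On unequal monitoring.** A reader might infer that SAE capture depends on contacts that only the intervention arm has. The article does not support that. PCPs document all SAEs in both arms, control patients remain under their PCP's care, and both arms complete PHQ-9 and OASIS at T1 and T2. The extra monitoring is part of the intervention under test, and recording of deaths is unlikely to depend much on telephone calls. What remains is a difference in the intensity of scheduled symptom monitoring, relevant to symptom-based SAEs.

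**On a biased analysis or an unblinded PI.** A reader might also infer that a biased comparison of SAEs is planned, or that a PI who knows the allocation could hold events back. The article lists SAEs in neither the outcomes nor the statistical analysis, and it does not state whether the PI is blinded. The randomization result is said to go to the regional physicians' association and the practices; the PI is not named as a recipient. Neither inference is supported.

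**Conclusion.** The concern holds as a contradiction in stated wording. On its natural reading, the SAE sentence makes the board's evaluation depend on the PI's discretion, which defeats the two-person check it is meant to secure, and the DSMB section does not cure this. The conclusion rests on that reading. On the milder reading the sentence still needs correcting, because it does not exclude the stronger one. Nothing in the article suggests that events have been or would be withheld.

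The difference in monitoring is a secondary caution for the board's reading of symptom-based SAEs by arm: 21 (or 14) scheduled contacts against none of that kind described in the control arm, with an effect on the counts that cannot be calculated. The count of MA calls, 17 in one place and 10 in another, must be reconciled in any case.

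**What to change.** 1. **Participation discontinuation:** delete the clause on the PI's discretion. Suggested replacement: *Every SAE that a PCP documents is evaluated by the PI and is also reported to the DSMB for its own evaluation.*
2. **Data safety and monitoring board:** say the same. Suggested addition: *For each of its two meetings a year, the DSMB receives a listing, by arm, of every SAE documented since the previous one.*
3. **Reading the listings:** show SAEs by arm beside PHQ-9 and OASIS at T1 and T2, with the number of respondents per arm. These are already collected in the same way in both arms and give the board a comparison that does not depend on the calls. They supplement the SAE listing and do not replace it, since they are taken only at 6 and 12 months.
4. **Call count:** reconcile the abstract with the section Intervention group.

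The cost is a few words of protocol text and line listings for two meetings a year. Item 3 needs no new measurement, but it does need an extract for the board, because the section Data collection and transmission does not name the DSMB as a recipient. By-arm listings should go to the board alone, so that the blind data review planned before the models are fixed is not compromised.

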### Accompanying studies

#### Health economic evaluation

Health economic evaluation includes the analysis of health service use, health care costs, as well as cost-effectiveness. Evaluation of health care costs will be conducted from the perspective of the health insurance fund and will be based on secondary data. To analyze cost-effectiveness the incremental cost effectiveness ratio (ICER) will be calculated, which is the ratio of the difference in mean health care costs and quality-adjusted life years (QALYs) between IG and CG after 12 months of intervention. QALYs be will calculated based on health-related quality of life measured with the EQ-5D-5 L-Index (primary data) and its German value set developed by Ludwig et al. [52].

#### Process evaluation

Comprehensive qualitative-quantitative evaluation is used to depict the processes involved in implementing primary care-based case management [53], whereby the qualitative analysis has priority.

The qualitative part includes the evaluation of communication and collaboration among participants, feasibility, and factors that support and inhibit the implementation of eHealth-supported primary care-based case management in patients, PCP, and MA.

For the quantitative part, participants (patients, PCP, MA) will be required to fill in a questionnaire at the beginning of the study on their acceptance of novel therapies and their attitudes towards and expectations of eHealth-supported therapy. After 6 months, the participants will evaluate the training, which was carried out using the online platform. At the end of the study (after 12 months), a survey will be conducted on various aspects concerning the implementation of the new treatment, including the degree of utilization (proportion of patients who received which therapy and how often), feasibility (protocol-compliant implementation), and saturation. Using data from the Embloom platform's initial use, continued use and reach of the program will be analyzed.

### Materials and methods

The recruitment for the qualitative interviews will be a random sample among study participants. Qualitative interviews and focus group discussions will be conducted using a semi-structured interview guideline. The guideline will be developed, piloted, and adapted on the basis of a literature search. Individual interviews will take place with about 20–30 patients, and expert interviews with approximately 10–15 PCPs and 10–15 MAs from the IG. Three-to-five focus group discussions will be held with 15–20 PCPs and 15–20 MAs (mono- and interdisciplinary) at the end of the study. The data will then be transcribed verbatim and the transcripts checked for accuracy. Participants’ names and further details that could be used for identification will be changed. With the support of commonly used software programs (e.g. MAXQDA), transcripts will be analyzed using qualitative content analysis.

For the quantitative part, self-developed questionnaires will be filled in by patients, PCPs, and MAs. To develop the questionnaire, a literature review was carried out and the results checked to ensure they are in line with the aims of the PREMA study. The questionnaire will then be adapted and pilot tested again. Commonly used software programs (e.g. SPSS) will be employed to conduct descriptive and regression analysis of the primary data. Triangulation of the qualitative and quantitative data will be performed if possible.

### Statistical planning and analysis

#### Power considerations and sample size calculation

Sample size calculation is based on power considerations regarding the statistical difference between the Intervention (PREMA) and treatment as usual (TAU). In a primary care setting, effect sizes of 0.2 standard deviation (SD) on the primary outcome were regarded as relevant. This effect size was the basis for our sample size calculation. Assuming a desired power of 0.9, a type 1 error of 0.05 (two-sided) and a correlation of the baseline values with the primary outcome of 0.5, a sample size of 395 patients per study arm would be necessary. Considering the hierarchical data structure defined by the cluster randomization, an average cluster size of ten patients per primary care practice and an intra-cluster-correlation coefficient (ICC) of 0.05, the design effect would be 1.45. Therefore, the necessary sample size per study arm increases to 590 patients in 59 primary care practices (in total, 1180 patients, 118 practices). Assuming a drop-out rate of 20% of practices and patients, we aim at recruiting 1844 patients in 148 primary care practices. This corresponds to 12.5 patients on average per primary care practice.

#### Statistical analysis for primary and secondary outcomes

Baseline characteristics of primary care practices and patients will be described using relevant descriptive statistics. The primary analysis follows the “intention-to-treat” principle and will be based on all available data of all included patients. Main outcome is the Mental Health Index 5 (MHI 5) score at baseline (T0) and 6 (T1) and 12 (T2) months after.

The score will be analysed as differences to baseline. For the analysis of the intervention effect, a linear mixed model (LMM), taking the hierarchical data structure into account, will be adapted. The patients and the GP practices they are nested in are included in the LMM as random factors; the practice location (urban versus rural), the baseline value of the score, as well as the treatment group and the time of measurement are included as fixed factors. Fixed-effects estimators are reported with 95% confidence intervals. If necessary, a sensitivity analysis with multiple imputation of missing values will be conducted.

The secondary outcomes will also be described using relevant descriptive statistics. Continuous variables will be analysed with LMMs and for dichotomous outcomes mixed logistic regression models will be performed. The other model parameters will be set as in the primary endpoint analysis.

The analyses will be performed using R (3.4.4 or newer) or Stata (14.2 or newer). All tests will be two-sided with alpha = 0.05.

A more detailed description of all analyses will be found in the statistical analysis plan, which will be written prior to the commencement of the analyses. The final definition of the statistical models will be performed after a blind review of the study data.

For the health economic evaluation, differences in mean health care costs between IG and CG will also be analysed by implementing linear mixed regression models to consider for several time points per respondent and for the underlying cluster structure. Thereby, non-parametric bootstrapping will allow calculation of unbiased standard errors despite the well-known skewness of health care cost.

For analysing the statistical uncertainty of the ICER, net benefit regression will be implemented in order to construct cost-effectiveness acceptability curves (CEAC).

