### Study procedures and timing schedule

The baseline assessment (T0) takes place by online self-reported questionnaires.

In the IG, the MA’s first telephone contact with the patient is scheduled for week 2 after the primary care practice is allocated to the IG; the PREMA sessions with the PCP start in week 3. In the CG, patients receive TAU.

The primary outcome (MHI-5) will be assessed by self-reported online questionnaires at baseline (T0) and 6 months (T1) and 12 months (T2) after baseline. Secondary outcomes will be assessed at baseline (T0) and 6 months (T1) and 12 months (T2) after baseline. The initial screening measures for depression (PHQ-9) and panic disorder (OASIS) will be repeated at T1 and T2.

For a detailed description of study activities and the components of the intervention, see Fig. 1 and Table 1.

**Table 1 Tab1:** Outcome parameters

Indicator	Instrument	Time point				Data source
		T_−1_	T_0_	T_1_	T_2_	
Screening and diagnosis	OASIS, PHQ-9, ICD-10 checklist	x				Primary care physician/diagnostic interview
Mental health (depression and panic disorder)	Mental Health Index-5 (MHI-5)		x	x	x	Patient assessment via questionnaire
Depression level	PHQ-9			x	x	Patient assessment via questionnaire
Anxiety level	OASIS			x	x	Patient assessment via questionnaire
Severity of panic attacks	Panic and Agoraphobia scale (PAS)		x	x	x	Patient assessment via questionnaire
Avoidance behaviour	Mobility Inventory for Agoraphobia (MIA)		x	x	x	Patient assessment via questionnaire
Quality of care	Patient Assessment of Chronic Illness Care (PACIC)		x	x	x	Patient assessment via questionnaire
Medication adherence	Adherence score		x	x	x	Patient assessment via questionnaire
Quality of life	EQ-5D-5 L index		x	x	x	Patient assessment via questionnaire
Comorbidity	Elixhauser index		x	x	x	Routine data
Health service use	Number of inpatient hospitalizations, days of inpatient hospitalizations, outpatient medical treatment, medication (defined daily dose, DDD)		x	x	x	Routine data
Sick leave	Days of inability to work, sickness benefit, rehab		x	x	x	Routine data
Health care costs	Inpatient hospital care costs, inpatient rehabilitation costs, outpatient (ambulatory) services and primary care costs, costs for medical supplies, costs for drugs, sick pay costs, total health care costs		x	x	x	Routine data
Acceptance, attitude, expectations, feasibility, training, communication, implementation, work satisfaction	Ad hoc items		x	x	x	Primary data

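### The primary model is valid and meets its power target, but could also adjust for diagnosis and the screening PHQ-9 and OASIS scores already recorded before allocation

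*Protocol article*

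**What the plan says.** In the protocol article, the section on statistical analysis for primary and secondary outcomes specifies a linear mixed model for change in MHI-5 from baseline. Patients and practices are random factors, and the fixed factors are "the practice location (urban versus rural), the baseline value of the score, as well as the treatment group and the time of measurement". Models for secondary outcomes take their other settings from this one. The section leaves further detail to a statistical analysis plan, and the final form of the models to a blind review of the data.

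Table 1 lists "OASIS, PHQ-9, ICD-10 checklist" at T−1. The section on screening and recruitment describes screening with both scales and confirmation of the diagnosis by the physician. The practice is allocated only once 12–13 patients are included or three months have passed. These variables are therefore fixed before allocation.

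The eligibility criteria admit patients with panic disorder, depression or both. The Intervention group section adapts part of the content to the diagnosis, including the monitoring checklist: "JAMoL [38] for patients with PD/AG, DeMoL [39] for Patients with depression". Randomisation is stratified by urban or rural practice only.

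The sample size section rests on these inputs: "effect sizes of 0.2 standard deviation (SD) on the primary outcome were regarded as relevant"; "a correlation of the baseline values with the primary outcome of 0.5"; and the result "a sample size of 395 patients per study arm would be necessary".

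**The concern.** The planned baseline correlation of 0.5 means that baseline MHI-5 explains 25% of outcome variance and leaves 75% unexplained. Diagnosis and the two symptom scores are plausible predictors of later MHI-5, and they cost nothing more to collect. Leaving them out may forgo some precision. Neither the stratification nor the model accounts for diagnosis mix, which may differ between practices and, by chance, between arms.

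Timing also matters. If covariates are first chosen at the blind review, the choice is made with outcome data in view, even though allocation is masked. Naming them beforehand avoids any question about how they were selected.

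**Working it through.** **Inputs from the article:** effect 0.2 SD; power 0.9; two-sided alpha 0.05; baseline correlation 0.5; 10 patients per practice; ICC 0.05; 590 patients in 59 practices per arm; 20% drop-out of practices and of patients.

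**Step 1: the plan's own figures.**
- Residual variance after baseline adjustment: 1 − 0.5² = 0.75.
- Patients per arm: 2 × (1.960 + 1.282)² × 0.75 / 0.2² ≈ 394.0, rounded up to 395. This matches.
- Design effect: 1 + (10 − 1) × 0.05 = 1.45. This matches.
- 395 × 1.45 = 572.75 per arm. The plan states 590, which is 17.25 more and slightly conservative.
- To recruit: 1180 / (0.8 × 0.8) = 1843.75, so 1844 patients; 118 / 0.8 = 147.5, so 148 practices. Both match.

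**Step 2: power of the stated model at 590 per arm.** Φ(0.2 / √(2 × 0.75 × 1.45 / 590) − 1.96) = Φ(3.294 − 1.96) = 0.909. There is no shortfall.

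**Step 3: possible gain.** The documents give no correlation of T−1 PHQ-9, OASIS or diagnosis with follow-up MHI-5. The extra share of variance explained, x, is therefore an assumption. The design effect is held at 1.45.
- Power = Φ(0.2 / √(2 × (0.75 − x) × 1.45 / 590) − 1.96)
- Gain in effective sample size = 0.75 / (0.75 − x) − 1

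| x (assumed) | Residual variance | Gain in effective n | Equivalent patients of 1180 | Power |
|---|---|---|---|---|
| 0 | 0.75 | 0% | 0 | 0.909 |
| 0.01 | 0.74 | 1.4% | 16 | 0.912 |
| 0.03 | 0.72 | 4.2% | 49 | 0.920 |
| 0.05 | 0.70 | 7.1% | 84 | 0.926 |

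**Step 4: how overlap with baseline MHI-5 limits the gain.** For one added covariate with correlation r₂ to the outcome and r₁₂ to baseline MHI-5, R² = (0.25 + r₂² − 2 × 0.5 × r₂ × r₁₂) / (1 − r₁₂²).
- r₂ = 0.3, r₁₂ = 0.6: R² = 0.16 / 0.64 = 0.25, so no gain.
- r₂ = 0.4, r₁₂ = 0.5: R² = 0.21 / 0.75 = 0.28, power 0.92.
- r₂ = 0.5, r₁₂ = 0.4: R² = 0.30 / 0.84 = 0.357, power 0.945. This was the most favourable case tried. It needs a covariate that predicts MHI-5 as well as MHI-5's own baseline does while overlapping with it only moderately.

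**Step 5: precision of an effect by diagnosis.** Assume, for illustration, two groups of equal size with no comorbid patients: 295 per arm and five per practice in each group.
- Design effect: 1 + 4 × 0.05 = 1.20. SE = √(2 × 0.75 × 1.20 / 295) = 0.078, so the 95% CI half-width within a group is 0.15 SD.
- Difference in effect between groups, treated as independent: 1.96 × √2 × 0.078 = 0.22 SD.
- Same difference when both groups share practices, so that the practice effect cancels: 1.96 × √(4 × 0.75 × 0.95 / 295) = 0.19 SD.

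Either half-width is about as large as the whole 0.2 SD target effect.

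**The case against.** The strongest objection is that this is a preference about covariates. The article says that an analysis plan will follow and that the models are settled after a blind review. Extra prognostic terms and subgroup analyses are the kind of detail left to such a plan, and the unseen plan may already include them. That stands, and it is why the point cannot be called an omission or a contradiction. It does not remove the benefit of fixing the covariates early, because the article does give a concrete list and these variables are not on it.

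It can also be said that the gain may be negligible. MHI-5 was chosen to reflect both depression and panic disorder, so its baseline value overlaps with PHQ-9 and OASIS, and the eligibility cut-offs (PHQ-9 from 9 to 22, OASIS at least 8) narrow the range of those scores. This stands too, so the range must start at zero.

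A reader might infer three stronger claims, which the documents do not support:
- **That the comparison is biased.** Allocation is random, and chance imbalance in diagnosis mix is covered by the confidence interval.
- **That the trial is underpowered.** The sample size relies only on baseline MHI-5, which is in the model, and power is above target.
- **That two separate populations are wrongly pooled.** Patients may have both diagnoses, and all intervention patients get the same structure of sessions, calls and platform. The stated aim is the average effect in this mixed group, and the Discussion concedes that the outcome is not specific to a diagnosis.

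**Conclusion.** The stated model is sound and meets its power target. The point is a minor improvement: three variables already recorded before allocation could be added as covariates. On an assumed 0 to 5% of additional variance explained, power at 590 per arm is 0.909 to 0.926, at most 1.7 percentage points more. The result rests on the plan's correlation of 0.5, its ICC of 0.05 and a design effect held at 1.45. The true gain could be nil.

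The second benefit, protection against chance imbalance in diagnosis mix, cannot be put into figures because the documents give no expected mix.

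A main effect of diagnosis adjusts only for level. It does not show whether the intervention works equally well in each diagnosis. That needs a treatment-by-diagnosis estimate, which would be too imprecise here to carry more than supportive weight.

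**What to change.** Before the blind review, state in the analysis plan that the primary linear mixed model also includes, as fixed covariates:
- diagnosis group in three categories: PD/AG only, depression only, both;
- the T−1 PHQ-9 score;
- the T−1 OASIS score.

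The primary outcome, the treatment contrast and the primary test stay as they are. If the effect by diagnosis is of interest, and the plan does not already provide for it, report it with confidence intervals from a treatment-by-diagnosis term and label it supportive.

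The cost is one sentence of model specification. No new data are needed, and the covariates add four parameters (two for diagnosis, one for each score), which is immaterial with about 1180 analysed patients.
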